### Statistical analysis

2.8

The analyses of this study will adhere to the recommended guidelines outlined in the CONSORT 2022 statement for reporting outcomes in clinical trial reports (40).

Dataset populations include the intention to treat (ITT) analysis population (all randomized children), the safety analysis (SAF) population (ITT population with documentation of at least one administration of study product), full analysis (FAS) population (all randomized children completing both food challenges), and the per protocol (PP) population (FAS subjects completing the study with no major protocol violations which are believed to impact the primary endpoint).

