### Sample size considerations

2.3

A maximum sample size of 60 children with one allergic reaction to the Test Formula would support the lower bound of the two-sided 95% confidence interval (CI) for the proportion of children who pass the food challenge to be at least 90%, meeting the established hypoallergenicity criteria (14). Allowing for a 10% drop-out rate, approximately 67 children will be enrolled. A sample size of 42 children with no allergic reactions to the HRF-HMO would support the lower bound of the two-sided 95% CI for the non-allergic reaction rate to be at least 90%. Therefore, an interim analysis is planned when 42 completed children in the full analysis set is reached. An external Data Monitoring Committee (DMC), composed of two independent experts in pediatric allergy and one independent expert statistician, will be responsible for reviewing the interim analysis results during a closed session. The DMC will then issue a written recommendation following a pre-specified decision tree stated in the DMC charter. The study may be stopped for success if no reactions have been observed after 42 children complete both food challenges. If one allergic reaction has been observed with the HRF-HMO during the DBPCFC, recruitment will continue to achieve 60 completers of the two food challenges. If two or more allergic reactions are observed with the HRF-HMO during the DBPCFC, the study may be stopped for futility.

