### Randomization and blinding

2.4

Upon obtaining informed consent by the investigators, eligible children will be randomized to one of the two following sequences for the DBPCFC: HRF-HMO followed by AAF-HMO or AAF-HMO followed by HRF-HMO. Randomization will be conducted in a 1:1 ratio using the Medidata Rave “Randomization and Trial Supply Management” (RTSM) technology. RTSM system automates patient randomization, ensures allocation concealment and maintains study blinding.

During the food challenge, the identity of the products will be blinded to the children, caregivers, investigators, site personnel, Contract Research Organization managing the study, and the sponsor (except the manufacturing site, supply, and quality managers). Study formulas will be prepared and administered to participants by a staff member who is not involved in the study assessments and is trained on proper preparation. The products will be packaged and labeled identically but will be distinguishable by unique codes affixed on the primary packaging. Individual coding of cartons will be used to prevent unblinding in case of emergency unblinding. Unblinding of individual coding may be requested by investigators in case of serious adverse events suspected to be related to the investigational product and requiring knowledge of the study product administered. The home usage phase is an open-label phase without blinding.

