### Study procedures

2.6

Study visits (V) and procedures are shown in Table 2. After enrollment, there will be 2 visits corresponding to the two oral food challenges, scheduled 2–7 days apart, followed by a final visit 1–2 weeks after the end of the at-home phase.

**TABLE 2 T2:** Study visits and procedures.

Visit	V1	V2	V3	Open challenge	V4
Study day	Study day 0	V1 + 3–28 days	V2 + 2–7 days	After V3 for 7 days	V3 + 8–14 days
Informed consent	X				
Assign subject number	X				
Inclusion-exclusion criteria	X				
Demographic information	X				
Medical history	X				
Physical exam, weight, vital signs		X	X		X
Height/length	X				
Randomization		X			
DBPCFC		X	X		
Product dispensing			X		X (if desired)
HRF-HMO administration				Daily	Check compliance
Digestive symptoms and formula intake record				Daily	Check record
Cow’s milk elimination diet	→	→	→	→	→
Concomitant diet and treatment	→	→	→	→	→
Adverse event record	→	→	→	→	→

DBPCFC, double-blind placebo-controlled food challenge; HRF-HMO, hydrolyzed rice protein-based formula containing two manufactured HMOs; V, visit.

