#### Double-blind placebo-controlled food challenge (DBPCFC)

2.6.1

The food challenge will be performed in a healthy child and will be postponed if the child is sick or if antihistamines or oral steroids were used 7 and 14 days before the challenge, respectively. The timing of the DBPCFC will be planned around the child’s normal schedule. Parents will be advised to feed their child a light non-fatty meal (about half of the usual portion) approximately 2 h before each test, and no foods or drinks should be consumed after this meal until the completion of the test procedure. Parents will also maintain a strict cow’s milk elimination diet for their children throughout the study period including during the DBPCFC.

During the food challenge, children will be fed increasing volumes of formula at intervals of at least 20 min, until reaching the target volume. The total volume is equivalent to an age-appropriate serving size as per expert recommendations (34, 37, 38), and will be a minimum of 180 mL (up to 210 mL) for infants below 1 year, and a minimum of 200 mL (up to 240 mL) for children ≥1 year, according to their usual serving size. If a child is not able to drink the total volume, a re-attempted feeding after a short break or a repeat of the test on a later date will be proposed, at the discretion of the investigator. Table 3 summarizes the dosing schedule during the food challenge, per age group.

**TABLE 3 T3:** Formula volumes and corresponding protein doses per age group.

Dose number	Infants < 1 year		Children ≥ 1 year		Timepoint (minutes)
	Protein dose (mg)	Feeding volume (mL)	Protein dose (mg)	Feeding volume (mL)	
1	31	2	31	2	0
2	101	7	101	7	20
3	307	20	307	20	40
4	920	60	1074	70	60
5	1381–1841	90–120	1534–2148	100–140	80
Cumulative dose/volume	2740–3200 mg	∼180–210 mL	3047–3661 mg	∼200–240 mL	1 h 20 min

Before each dose, vital signs will be measured and a physical examination completed to determine whether any change in the child’s clinical status has occurred in conjunction with the DBPCFC.

The following definitions will be used for to determine the outcome of the DBPCFC:

To pass the food challenge means to consume the total volume of formula and display no dose-limiting allergic reaction to any of the doses.To fail the food challenge means to display a dose-limiting allergic reaction during the food challenge.To complete the food challenge means to either pass or fail the test.

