#### Primary outcome measure

2.7.1

The primary outcome is the number of children who pass the DBPCFC with HRF-HMO. Passing a food challenge means the total volume of formula is consumed and no dose-limiting allergic reaction to any of the doses is displayed. Failing a food challenge means displaying a dose-limiting allergic reaction during the food challenge. If a child does not achieve the total volume consumption because of a reason other than an allergic reaction, such as inability to drink the formula, this will be considered an incomplete challenge, not a failure to the DBPCFC. Standardized criteria will be used by all investigators to assess the “pass/fail status” of the food challenge (34, 37, 38).

The primary outcome is based on international criteria of hypoallergenicity (14). A formula is considered hypoallergenic if at least 90% of children with CMA can tolerate it with no allergic reactions (14).

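### The completer-of-both-challenges set can leave out a known HRF-HMO failure, and the article does not say which set decides success

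*Protocol article*

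**What the plan says.** All references are to the protocol article.

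- **Endpoint (2.7.1).** The primary outcome counts children who pass the HRF-HMO challenge. A challenge stopped short for a reason other than an allergic reaction is set apart: "this will be considered an incomplete challenge, not a failure to the DBPCFC".
- **Completion (2.6.1).** "To complete the food challenge means to either pass or fail the test". A reactor therefore completes the challenge in which the reaction occurs.
- **Analysis sets (2.8).** "full analysis (FAS) population (all randomized children completing both food challenges". The per-protocol set is a subset of the FAS. ITT is every randomized child.
- **Sequence (2.4).** "Randomization will be conducted in a 1:1 ratio" to "HRF-HMO followed by AAF-HMO or AAF-HMO followed by HRF-HMO".
- **Interim and final counts (2.3).** "an interim analysis is planned when 42 completed children in the full analysis set is reached". After one HRF-HMO reaction, recruitment goes on to 60 children who have completed both challenges.
- **Success criterion (2.8.1).** The lower limit of the two-sided 95% interval for the HRF-HMO pass proportion must be at least 90%, at interim and final. No analysis set is named.
- **Presentation (2.8.2).** Primary and secondary results are shown in ITT and PP. The FAS is not mentioned there.
- **Timing (2.6 and 2.6.1).** "there will be 2 visits corresponding to the two oral food challenges, scheduled 2–7 days apart". A challenge is postponed if "antihistamines or oral steroids were used 7 and 14 days before the challenge, respectively".

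**The concern.** The endpoint needs one challenge result, but membership of the FAS needs two. Take a child randomized to HRF-HMO first who fails at V2 and does not go on to pass or fail AAF-HMO at V3. The primary question has been answered for this child, and the answer is a failure. Because 42 and 60 are counted in completers of both challenges, the child is absent from numerator and denominator, and another child fills the place.

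Loss between V2 and V3 may not be independent of the HRF-HMO result. A reactor treated with an antihistamine at V2 has, at best, the last day of the 2–7 day window before the 7-day restriction ends. After an oral steroid the 14-day restriction outlasts the window. A child who passes at V2 faces no such treatment-related delay. This makes late or missed second challenges more likely in treated reactors.

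At stake is a hypoallergenicity claim that allows no reaction in 42 children, or one in 60.

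**Working it through.** **1. The plan's own figures.** Exact (Clopper-Pearson) two-sided 95% lower limit for x passes in n: the 2.5% quantile of Beta(x, n − x + 1). The article does not name the interval method; Wilson limits give the same verdicts at the four counts below.

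| Passes/n | Lower limit | Consequence under 2.3 and 2.8.1 |
|---|---|---|
| 42/42 | 91.6% | may stop for success |
| 41/42 | 87.4% | continue to 60 |
| 59/60 | 91.1% | success |
| 58/60 | 88.5% | not success |

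The stated 42 (no reaction) and 60 (one reaction) both reproduce, as does enrolment: 60/0.90 = 66.7, rounded up to 67.

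**2. Restoring one omitted reactor.** If the child is added rather than substituted, 42/42 becomes 42/43 (87.7%) and 59/60 becomes 59/61 (88.7%). Both are below 90%.

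**3. Probability of success under the rule.** Let r be the reaction rate in the analysed set. Success is no reaction in 42, or one in 42 and none in the next 18. Two or more reactions are taken as a stop.

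P = (1 − r)^42 + 42·r·(1 − r)^41·(1 − r)^18

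At r = 0.10: 0.0120 + 0.0084 = 0.0204, or 2.0%.

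**4. Effect of loss after the first challenge.** Assume half of the children receive HRF-HMO first. Let d be the share of HRF-first reactors, and e the share of HRF-first passers, who never complete AAF-HMO. With no other losses, the reaction rate in the FAS is

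r_F = r(1 − d/2) / [r(1 − d/2) + (1 − r)(1 − e/2)]

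Example with r = 0.10, d = 0.50, e = 0: 0.075 / (0.075 + 0.900) = 0.0769, and P = 0.0347 + 0.0287 = 0.0634.
Example with d = 0.50, e = 0.20: 0.075 / (0.075 + 0.810) = 0.0847, and P = 0.0243 + 0.0192 = 0.0434.

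True reaction rate 10%, so any success is wrong:

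| Reactors lost (d) | Passers lost (e) | Pass rate in FAS | Wrong success |
|---|---|---|---|
| 0% | 0% | 90.0% | 2.0% |
| 10% | 10% | 90.0% | 2.0% |
| 10% | 0% | 90.5% | 2.6% |
| 25% | 0% | 91.1% | 3.6% |
| 25% | 20% | 90.3% | 2.3% |
| 50% | 20% | 91.5% | 4.3% |
| 50% | 0% | 92.3% | 6.3% |
| 100% | 0% | 94.7% | 19.4% |

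The article gives neither d nor e, so every row but the first rests on an assumed loss. Equal loss leaves the error rate unchanged; only an excess among reactors raises it.

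**The case against.** **ITT keeps the reactor.** Section 2.8.2 names ITT as one of the two sets for the primary outcome. This stands, and it rules out saying that the plan deletes such failures from its decisive analysis. It does not settle the matter: 2.8.1 names no set, 2.3 counts in completers of both challenges, and PP repeats the exclusion.

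**Section 2.3 may use the FAS only for timing.** Its decision wording speaks of reactions observed, which can include a reaction in a child who did not complete both challenges, and the decision tree itself is in a DMC charter that is not shown. This is a fair reading. The other reading, that reactions are counted within the FAS, is equally open.

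**Postponed does not mean lost.** A reader might infer from the window and the wash-out that treated reactors must be excluded. The text does not support that. It postpones the challenge, no passage withdraws a child who fails the first one, and the FAS has no window condition, so a late second challenge still qualifies. The conflict makes loss more likely, not certain.

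**Passers are lost too.** The Discussion names the taste of the AAF as an obstacle to consuming it. Losing passers lowers the pass rate in the FAS, so upward bias is conditional.

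**A set requiring both challenges suits a placebo-controlled criterion.** That justifies keeping it as a supportive set, but not making an HRF-HMO result depend on the AAF-HMO result.

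**Conclusion.** The point holds in a limited form. The article states, rather than leaves open, that the FAS requires both challenges and that the interim and final counts use completers of both. It presents results in other sets and names none for the success criterion. On the FAS reading, a known HRF-HMO failure can be left out.

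At a true 10% reaction rate, wrong success rises from 2.0% to between 2.3% and 6.3% for the unequal losses shown with up to half of HRF-first reactors lost. The 19.4% needs every HRF-first reactor lost and no passer lost, and is an outer limit. These results rest on 1:1 sequences, losses only after a first HRF-HMO challenge, and assumed loss rates.

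A reader might also infer that one omitted reactor turns failure into success at either look. That is true at 60, but not at 42: there it turns a continuation into an early stop for success, and the continued trial could still succeed at 59/60.

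This should be fixed; confidence is medium, because the SAP and DMC charter may already name the deciding set.

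**What to change.** 1. In 2.8, define the primary set, at interim and final, as all randomized children with a pass or fail on the HRF-HMO challenge, whatever happens with AAF-HMO.
2. In 2.8.1, name that set in the success criterion. In 2.3, apply 42 and 60 to it, and state that every HRF-HMO failure counts. Align the presentation sets in 2.8.2, the SAP and the DMC charter.
3. Keep the both-challenges set as a supportive analysis.
4. Reconcile the V2–V3 window in 2.6 with the medication wash-out in 2.6.1. How to do so is a clinical matter for the sponsor and investigators.

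The cost of items 1 to 3 is wording, with no planned increase in sample size. The small downside is that some HRF-HMO results will have no paired AAF-HMO result.

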#### Primary outcome

2.8.1

The number and percentage of children who pass/fail the DBPCFC with the HRF-HMO will be presented. The two-sided 95% CI, and its corresponding *p*-value will be provided for the point estimates of the proportion of children with no allergic reactions to each formula during the food challenge. At both interim and final analysis, the study will be considered a success if the lower bound of the two-sided 95% confidence interval for the proportion of children who pass the food challenge with HRF-HMO is at least 90%.

#### Secondary outcomes

2.8.2

Secondary outcomes of gastrointestinal tolerance (stool frequency, stool consistency, gastrointestinal symptoms) collected during the at-home open challenge will be summarized descriptively. The incidence of adverse events and allergy-related symptoms will be summarized by study product (HRF-HMO and AAF-HMO) during the food challenge, and by period for HRF-HMO (during the food challenge and the at-home phase). Occurrence of adverse events, including any gastrointestinal, skin or respiratory symptoms, will be summarized in a table presenting frequency, severity, seriousness of adverse events, as well as their relationship to the assigned formulas.

The results of the primary and secondary outcomes will be presented in the ITT and PP populations.

#### Data management

2.8.3

Data management systems used in the RIGHT-HY study will comply with Good Clinical Practices, laws, and regulations. Data will be entered from the source document into an electronic Case Report Forms by the investigators. The gastrointestinal symptoms and formula intake record will be filled by the caregivers using paper questionnaires. The Clinical Data Manager will validate all data entered into the eCRF. Data discrepancies will trigger automatic queries, and if necessary, manual queries will be sent to the Investigator for clarification. All data modifications will be documented in an audit trail file.

Data will be periodically and blindly monitored throughout the study by the sponsor representatives to evaluate study progress and to verify quality and completeness of data collection.

## Discussion

3

We present the first study protocol evaluating the hypoallergenicity of a HRF containing two manufactured HMOs intended for the management of infants and children with CMA. The results of this study will support the safe use of HRF in children with CMA and provide evidence that this new HRF with HMOs meets the generally accepted criteria of hypoallergenicity. Providing families of non-breastfed infants with plant-based options that are not only palatable, but also supported by documented efficacy and safety is important.

The criteria for defining a formula as hypoallergenic have been established (14), and the design of this study adheres to those requirements. The rate of allergic reactions to the HRF-HMO will determine its hypoallergenicity under double-blinded controlled conditions. The 1-week open challenge phase will document the safety and gastrointestinal tolerance of the HRF-HMO in typical home use. Additional data on the growth, safety and tolerability of HRF-HMO will be collected over a 4-months period in a complementary study (NCT06633250), including an assessment of allergy symptoms and quality of life.

The addition of HMOs to HRFs could play a critical role in supporting gut health and immune health of non-breastfed infants with CMA. Preclinical data suggest that HMOs might attenuate allergic symptoms (41) and might promote tolerance development via interaction with dendritic cells (42). In clinical studies, the addition of 2’FL and LNnT to an eHF formula partially corrected the gut dysbiosis commonly seen in infants with CMA, which may affect the maturation of their immune system (31, 43, 44). Furthermore, the manufactured HMOs included in this formula could have a beneficial impact on the reduction of infections and antibiotic use, as observed in studies involving eHF and HMOs. These HMOs may also positively impact the long-term health trajectories of formula-fed infants. As popularity and usage of HRFs grow, future studies should investigate the impact of HMOs within the HRF matrix on other relevant outcomes such as clinical infections and changes in gut microbiota.

The main strengths of this study lie in its rigorous methodology and novelty. Notably, the study features a well-designed food challenge protocol, in line with recommendations for hypoallergenicity studies. The randomized, controlled, double-blind design minimizes the risk for bias and strengthens the validity of study results. Furthermore, the multicenter and multinational approach of the study will enhance the generalizability of the findings. Importantly, this is the first study to generate data on the hypoallergenicity of a HRF containing HMOs. Limitations of this study include the use of an AAF as a control during the DBPCFC, which may affect the ability of some children to consume it during the food challenge due to its specific taste. However, the use of AAF is considered a safer option during the food challenge as up to 10% of children with CMA may experience an allergic reaction to eHFs.
